## Introduction

Population ageing has seen substantial growth in the 21*st* century, with many countries seeing a shift in population distribution towards older ages [1]. The World Health Organization (WHO) projects that the population of individuals aged 60 years and above will double and reach 2.1 billion by 2050 [1]. In Singapore, the proportion of people aged 60 and above is predicted to rise from 13.3 % in 2010 to 31.9 % in 2050 [2]. Accelerated population ageing represents a global challenge, as ageing has been widely associated with cognitive impairment [3]. For example, a meta-analysis revealed that the prevalence of dementia doubled with every 6.7 years increment in age in South-East Asia [4]. In turn, age-related cognitive impairment has been linked with a multitude of risk factors and health concerns, including psychosocial variables, speech and neurological deterioration. Specifically, psychosocial variables pertain to an individual's psychological and social state which in this case can positively or negatively influence their cognitive health. For instance, depression and anxiety have been associated with cognitive deficits in older adults [5,6]. Cognitive impairment has also been linked to linguistic features including pauses as well as slower speech and articulation rates [7,8]. Given the wide range of health issues associated with ageing, the rapid pace of population ageing prompts a pressing need to better understand these factors.

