## Research hypotheses

We hypothesized that: (1) there would be some cognitive decline in participants in the CHI study cohort after 3 years. Specifically, (i) there would be a larger proportion of MCI and dementia cases in the CHI study cohort after 3 years and (ii) cognitive scores of participants in the LFC study would be worse than their respective scores in the CHI study after controlling for age. We also hypothesized that (2) there would be differences in cognitive scores, psychosocial outcomes and speech characteristics between groups of normal ageing, MCI and dementia, and (3) selected neuroimaging, psychosocial and speech markers would be associated with cognitive decline and other psychosocial outcomes. Specifically, we hypothesized that (i) slower speech rates and more abstract nouns and verbs would be related to greater cognitive decline, (ii) patterns of functional and structural connectomes would be associated with cognitive decline as well as depression and anxiety symptoms. Lastly, we hypothesized that 4) participants who had been involved in NPIs from the CHI study would be likely to retain or show improvement in cognitive function and psychosocial outcomes when assessed during the LFC study. In support of this hypothesis, Ng et al. conducted a 5-year follow up and found that participants who had previously participated in NPIs had cognitive improvements as compared to control participants who did not participate in NPIs [16]. As such, the effects from previous NPIs should be retained when examined in the LFC Study. This paper describes the LFC study design, setting and procedures.

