### Visit 1A

The first visit, visit 1A, was conducted at HAAC. Trained assessors, consisting of research assistants and a research nurse, recorded changes to the participant's socio-demographic and personal medical history information based on their CHI study records. Thereafter, participants underwent a safety screening questionnaire to gather information regarding their Magnetic Resonance Imaging (MRI) contraindications, such as metallic bodily implants, pacemakers and/or claustrophobia. The Barthel's Activities of Daily Living (BADL), instrumental Activities of Daily Living (iADL), the Clinical Dementia Rating (CDR) and neuropsychological tests were subsequently administered to the participants by trained assessors. A segment in the CDR required a face-to-face or phone interview with a family member or caregiver of the participants. As such, participants were requested to nominate a family member, who acted as an informant and provided objective information regarding the participant's cognition and daily functioning. The informant was first required to read and complete an Informant Information Sheet (IIS) and Consent Form before an interview was arranged with them. Lastly, participants who agreed to take part in a Free-Flowing Speech (FFS) segment were instructed to speak freely about topics of their choice, without any constraints for 15–20 min. They were allowed to speak using a language of their choice and their natural speech was audio recorded. Participants were also instructed to remain anonymous during the recording.

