### Visit 1B

The second visit, visit 1B, consisted of psychosocial questionnaires and could be completed either at home or at HAAC. Participants were encouraged to complete visit 1B on paper or online (i.e., using Qualtrics) at home. Those who opted to complete the questionnaires on paper were given the questionnaires during visit 1A. Participants were also given the option to mail their completed questionnaires to a given address, or physically pass the questionnaires back to the research team. If participants were unable to complete the questionnaires at home, visit 1B could be conducted face-to-face at HAAC. Both visits 1A and 1B could be conducted in English or Mandarin, depending on the participant's preference and comfortability with language.

### Visit 2

The last visit, visit 2, was an MRI scan conducted at NUS Clinical Imaging Research Centre (CIRC). Due to budget constraints, this visit was made available to only 300 selected participants. Prior to the scan, participants were briefed on the scan procedures, as well as its potential risks and discomforts. The scan lasted for approximately 30 min. Once the scan concluded, participants were able to request for a copy of the MRI scan images before leaving the centre.

Participants were reimbursed after each visit. Reimbursement for visits 1A, 1B and 2 was $5, $5 and $10, respectively. Fig. 1 below summarizes the flow of the different visits, as well as the different instruments administered during each visit. The instruments utilized in this study were developed through the multi-disciplinary liaison of co-investigators, which allowed for the collection of multi-disciplinary measures.

Fig. 1 shows the flow and instruments administered during each study visit. The visit flow is divided into 5 parts: an introductory phone call, informed consent-taking process, visit 1A, 1B and 2. Participants were introduced and invited to HAAC during an introductory phone call. For the informed consent-taking process at HAAC, their cognitive capacity was screened via MMSE as per NUS-IRB requirements before the study was explained to them and their written informed consent were taken. Visits 1A, 1B and 2 were completed subsequently, consisting of neuropsychological assessments, psychosocial questionnaires and an MRI scan respectively.

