Cognitive Functioning	Measures of cognitive functioning were as follows: (1) A locally modified and validated 30-point MMSE with local education and ethnic norms to assess global cognitive function [32,33]; (2) the 5-point CDR to measure cognitive and functional performance from interviews with participants and informants [34]; (3) a validated neurocognitive battery that measured auditory-verbal learning and short-term memory (Rey Auditory Verbal Learning Test), ability to hold and manipulate information in working memory (Digit Span Forward and Backward Task), selective visual attention (Colour Trails Test), visual-spatial abilities (Wechsler's Block Design), verbal fluency (Semantic Verbal Fluency—Animals) and selective attention as well as cognitive inhibition (Stroop Test Color and Word Test - Victoria Modification). Participants were diagnosed as either cognitively normal, MCI or dementia by a panel of expert clinician and psychologist.	1A
Free-Flowing Speech	Participants were asked to speak freely about a topic of their choice for 15–20 min. They were allowed to use a language of their choice and their speech will be audio recorded.	1A
Physical Activity	Physical activity level was measured by the 4-item International Physical Activity (short form) questionnaire [35]. Participants were asked to state the number of days and time they spent engaging in vigorous and moderate activities as well as walking and sitting. The questionnaire was validated with adults aged 18 to 65 across 12 countries, with an acceptable test-retest reliability of 0.74 [35].	1B

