## Data analysis

All demographic variables would be presented as descriptive summaries, such as means, standard deviations, median, standard errors and percentages, depending on the parametric/ non-parametric nature of the data. Non-parametric measures were normalized before being subjected to analyses.

To examine hypothesis 1, chi-square analyses were performed to investigate any changes in frequency of groups, i.e., normal ageing, MCI and dementia, across the 3-year period. Cognitive scores of participants from the LFC study were compared with their respective scores in the CHI study using dependent-samples *t*-tests.

As for hypothesis 2, potential differences of cognitive functioning, psychosocial outcomes and speech characteristics between groups, i.e., normal ageing, MCI and dementia, were analysed using independent-sample *t*-tests and Analysis of Variance (ANOVA).

To investigate hypothesis 3, cross-sectional brain-behaviour associations were examined via whole-brain approaches, n across various MRI modalities such as cortical thickness, structural connectivity resting state functional connectivity. Network-based statistics were used to identify structural and functional brain networks corresponding to behavioural and diagnostic variables. As for cortical thickness, whole-brain vertex-wise associations with behaviour will be analysed using the ‘standard linear regression’ module in the ‘BrainStat’ Python library [57]. The random field theory (RFT) correction, which corrects the probability of ever reporting a false positive result, was applied with a cluster-defining threshold of *p*<0.05.

Relationships between cognitive decline and various psychosocial outcomes such as depression and anxiety symptoms, quality of life and social connectedness were analysed using multiple regressions and structural equation models. Speech characteristics such as speech rate and concreteness were obtained after audio recordings are transcribed. Speech rates of various nouns and verbs were calculated by dividing the total number of nouns and verbs by the total number of minutes. Concreteness scores were obtained based on the concreteness ratings of 40,000 English words assembled by Brysbaert et al. [58]. Associations between these speech characteristics, cognitive decline and psychosocial outcomes were subsequently analysed using multiple regression analyses.

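### Speech could be recorded in any language, yet concreteness uses English word ratings and the stated rate counts only nouns and verbs: the speech analyses are open to language effects and do not isolate tempo

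*Protocol article*

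**What the plan says.** On the speech segment, the Visit 1A section of the protocol article says: "They were allowed to speak using a language of their choice and their natural speech was audio recorded". Table 2 under Outcome measures repeats the rule: "They were allowed to use a language of their choice and their speech will be audio recorded". Recordings in other languages are to be expected, because the Visit 1B section adds that "Both visits 1A and 1B could be conducted in English or Mandarin". The segment was optional, for "participants who agreed to take part in a Free-Flowing Speech (FFS) segment", and no number of recordings is given.

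On scoring, the Data analysis section says "Concreteness scores were obtained based on the concreteness ratings of 40,000 English words" and names no other ratings. It gives one rate formula: "Speech rates of various nouns and verbs were calculated by dividing the total number of nouns and verbs by the total number of minutes". These measures enter multiple regressions with cognitive decline and psychosocial outcomes (hypothesis 3), and t-tests and ANOVA across the diagnostic groups (hypothesis 2).

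Hypothesis 3(i), under Research hypotheses, is that "slower speech rates and more abstract nouns and verbs would be related to greater cognitive decline". The Introduction gives the rationale: "Cognitive impairment has also been linked to linguistic features including pauses as well as slower speech and articulation rates".

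**The concern.** There are two separate difficulties.

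First, collection and scoring do not fit together. An English rating list has no entry for a Mandarin word. A non-English recording must be dropped, translated, or left without a score. Dropping it selects participants by language. Translating it scores the translator's vocabulary. Leaving it unscored makes data missing by language. Whichever route is taken, the concreteness variable or its sample is tied to language. If language is also related to the outcome, an association with the speech marker can appear without any link between concreteness and decline.

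Second, a count of nouns and verbs per minute is not a tempo measure. It rises and falls with how much of the speech consists of nouns and verbs, and that share may differ between people and between languages. The hypothesis and its rationale are about slower speech and articulation.

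At stake is the interpretation of hypothesis 3(i) and of the speech comparisons in hypothesis 2. The Discussion expects the study's findings to inform interventions, with linguistic therapy as an example.

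**Working it through.** **The plan's own figure.** Study sample and participation criteria gives N = 550 for f² = 0.02, three predictors, α = 0.05 and 80% power. Using the noncentral F for the overall test, with 3 and N − 4 degrees of freedom and noncentrality 0.02 × N, the smallest N reaching 80% is 550 (power 0.801). At N = 653, power is 0.870. The figure reproduces and is not in dispute.

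**What the rate measures.** Nouns plus verbs per minute = words per minute × noun/verb share. The tempos and shares below are assumed, for illustration:

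| Words per minute | Share | Nouns + verbs per minute |
|---|---|---|
| 120 | 0.30 | 36 |
| 120 | 0.45 | 54 |
| 100 | 0.40 | 40 |

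At the same tempo of 120 the score runs from 36 to 54. The slower speaker in the last row (40) scores above the faster speaker in the first (36). The variable can therefore reverse the order of speaking speed, although it still depends partly on pace.

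**Loss of sample if only English recordings are scored.** Neither the number of recordings nor the language mix is given, so both are assumed. Power is for the same overall test at f² = 0.02.

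| Recordings assumed | English share assumed | N scored | Power |
|---|---|---|---|
| 550 | 80% | 440 | 0.70 |
| 550 | 50% | 275 | 0.47 |
| 653 | 80% | 522 | 0.78 |
| 653 | 60% | 391 | 0.64 |
| 653 | 40% | 261 | 0.45 |

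The loss depends on the test. A test of one coefficient in a three-predictor model needs 395 for 80% power at the same f². On that test 440 and 522 would suffice, 391 would fall just short, and 275 and 261 would not be enough.

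**Spurious association from language alone.** Suppose a proportion p speaks another language and the two groups differ by d₁ on the marker and d₂ on the outcome, in within-group SDs. Then

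r = p(1 − p)d₁d₂ / √[(1 + p(1 − p)d₁²)(1 + p(1 − p)d₂²)], and f² = r²/(1 − r²).

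Take p = 0.4 (assumed), so p(1 − p) = 0.24.

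- Gap in cognitive level equal to the marker gap:
  - d = 0.7: r = 0.1176/1.1176 = 0.105, f² = 0.011.
  - d = 1.0: r = 0.24/1.24 = 0.194, f² = 0.039.
- Smaller gap in 3-year decline, which is the outcome in hypothesis 3(i):
  - d₁ = 0.7, d₂ = 0.2: r = 0.0336/√(1.1176 × 1.0096) = 0.03, f² = 0.001.
  - d₁ = 1.0, d₂ = 0.3: r = 0.072/√(1.24 × 1.0216) = 0.06, f² = 0.004.

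The first pair is closer to hypothesis 2, which compares groups defined by current cognitive status. The second is closer to hypothesis 3(i). Both are unadjusted. If language acts through education or age, adjusting for those would shrink them.

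**The case against.** The strongest reply is that this is a condensed article. It lists no covariates for any speech regression: not age, education or sex, and not language. Transcript handling and covariate lists commonly sit in the full protocol or analysis plan. A reader might infer that the regressions leave language out. The text does not support that; it shows only that the handling of language is not stated. This part of the objection stands.

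A reader might also infer that hypothesis 3(i) is confounded. The documents give no language mix and no relation between language and cognition, so they support only that it is open to confounding. A gap in cognitive level need not carry over to a gap in decline, and with a modest gap in decline the spurious association falls well below the planned effect.

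On the rate, speech rate and concreteness are introduced as examples of speech characteristics, and the formula is for rates of nouns and verbs. It may be meant as a lexical measure beside an overall rate. A reader might conclude that the study does not measure speaking speed at all. That goes too far, because the stated variable is a partial proxy for pace.

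What remains does not rest on omission. The article fixes an English rating source for recordings that it allows in any language. The one rate formula that it gives mixes tempo with word-class share. A full protocol could add language handling, but the mismatch and the formula stand as written.

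**Conclusion.** The point holds in limited form. Followed as written, the rules make concreteness scores, or the sample that has them, depend on recording language. They also give a rate that does not isolate the slower speech predicted by hypothesis 3(i). The speech analyses under hypotheses 2 and 3(i) are open to confounding or selection by language.

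The size is unknown. The illustrations span a spurious f² of 0.001 to 0.039 against the planned 0.02, and power of 0.45 to 0.78 for the overall test if 20–60% of recordings cannot be scored. All of these rest on assumed language shares, recording counts and group gaps.

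This should be fixed, but it is not critical to the study. It concerns the speech parts of two of the four hypotheses, in an optional segment, and can be repaired from transcripts while analyses are still under way. The sample size calculation is correct and unaffected.

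**What to change.** - **Concreteness.** Score within language: English ratings for English recordings, and language-specific ratings for others where available. Where they are not, restrict the primary concreteness analysis to English recordings, report the N per language and limit the conclusion to English speakers. Restriction is itself selection by language, hence the limit on the conclusion. Keep any translated scoring as a sensitivity analysis only.
- **Models.** Include recording language as a covariate, or stratify by it, in every speech model. This covers the diagnostic-group comparisons under hypothesis 2, where a plain t-test cannot carry it.
- **Rate.** Define speech rate as total words (or syllables) per minute, standardised within language. Report noun and verb rates as separate lexical measures.

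The cost is a recount from the existing transcripts, one added covariate or stratum, and a smaller concreteness sample with less power. The Study progress section says that analyses are still ongoing, so the change can be made now.

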The Community Health and Intergenerational (CHI) baseline study (*n* = 993) was started in 2018 to study these age-related issues in the local context [9]. Participants of the CHI study consisted of community-dwelling older adults aged 60 to 91 from the Toh Yi estate in Singapore and other areas in a 10 km radius from the research site at Hannah Active Ageing Centre (HAAC). They underwent neuropsychological assessments, interviews, blood and dental plaque collection as well as cardiovascular examinations as per study procedures. These provided comprehensive assessments of the health profiles of participants as well as their baseline cognitive functioning and psychosocial outcomes. Data collection for the CHI Study began on 1*st* February 2018 and ended on 26*th* October 2021. Additionally, the CHI study acted as a recruitment platform for other randomized trials that investigate non-pharmacological interventions (NPIs). For example, studies conducted by Shefaly et al. [10] and Low et al. [11] investigated the effects of respective NPIs, including face-to-face mindfulness training and dietary counselling, on the well-being of older adults from the CHI study cohort. Participants who received the face-to-face mindfulness intervention expressed an improvement in their overall well-being and quality of life. Similarly, participants in the dietary counselling intervention group showed a significant increase in dietary quality and decrease in serum low density lipoprotein cholesterol level. Taken together, current evidence has shown that NPIs from the CHI study can be effective in improving the well-being of older adults.

Presently, we initiated a follow up to the CHI study — the Longitudinal Follow-up of the CHI (LFC) study. This was a 3-year follow-up of the CHI study cohort to examine longitudinal changes in their cognitive functioning and psychosocial outcomes, including depression and anxiety symptoms, sleep quality, life satisfaction, quality of life, attitudes towards ageing, social connectedness and perceived social support. Although such associations had been presented in studies examining Western populations, this inquiry remains understudied in the Asian population. Hence, it would be crucial to investigate how psychosocial variables change with time in this specific Asian cultural context, as this would contribute to existing literature regarding the course of ageing and its associated mental health concerns in the Singapore population.

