The LFC study also looked into the longitudinal associations of cognitive functioning and psychosocial outcomes with linguistics and neuroimaging measures. Significantly, the latter measure was not collected in the CHI study and thus the LFC study hoped to advance this area of research. The investigation of multimodal neuroimaging data would serve multiple objectives and allow us to test several hypotheses. First, it would enable us to develop brain-based prediction models so as to predict the wide array of cognitive and psychosocial outcomes that would be highly relevant in the geriatric mental health context. Next, such data could be used to study how certain lifestyle and psychosocial factors moderate age-related changes in the brain. Additionally, neuroimaging data could also be used as an external dataset to validate hypotheses and prediction models derived from other datasets. As for associations between linguistic measures and cognitive functioning, previous studies had shown that patients diagnosed with semantic dementia utilize more abstract nouns and verbs as well as slower speech rates [12,13]. This highlights the possibility that such deterioration in language might also be present at the mild cognitive impairment (MCI) stage, which occurs before the dementia stage. Studying these associations would then inform us about the aspects of language to target to slow down the onset of dementia. Additionally, the joint investigation of linguistics, neuroimaging and psychosocial measures in the context of age-related cognitive impairment are vital as such research is scarce in both local and global contexts. Given that these measures have been previously identified as risk factors for cognitive impairment, the LFC study looked to further supplement this area of literature [5], [6], [7], [8],[12], [13], [14], [15]. Lastly, the study also examined if participation in previous NPIs from the CHI study would prevent cognitive decline and improve psychosocial outcomes when assessed during the LFC study. This would be a valuable addition to the CHI study as long-term individual and overall effects of NPIs on cognitive decline and psychosocial outcomes can be analysed and reported, providing key insights into the longitudinal effects of NPIs.

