Lastly, to evaluate hypothesis 4, linear-mixed modelling and multivariate regression analyses were employed to examine the individual and overall effects of NPIs on cognitive functioning and psychosocial outcomes. P-values of <0.05 were considered statistically significant. Bonferroni corrections were conducted when applicable to reduce false positive rates.

Given that the LFC study has only recently completed data collection, data analyses are still ongoing and specific results are unavailable at the moment. Additionally, given that this is a protocol paper, the authors will focus more on the protocol rather than the results and findings.

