## Discussion

The LFC study aimed to better understand the ageing process and its associated health issues by examining longitudinal changes in participants’ cognitive functioning and psychosocial outcomes as compared to the baseline CHI study. The present study also hoped to improve the mental and physical well-being of the older population in Singapore by investigating the associations between cognitive decline, psychosocial outcomes, speech characteristics and neuroimaging data. Significantly, the joint collection and investigation of these variables was not typically conducted in other cohort studies, including the CHI study. As such, this provides invaluable information regarding speech characteristics and neuroimaging data across the whole spectrum of dementia, ie., normal ageing, MCI and dementia. Findings would then be used to devise new intervention strategies, such as linguistics therapy, benefitting the overall mental and cognitive health of the Singapore ageing population.

The LFC study also evaluated if the effects of NPIs on cognitive impairment and psychosocial outcomes were still present at follow-up. This constituted a more rigorous evaluation of NPIs, since it provided vital information as to whether the effects of NPIs were sustained after non-pharmacological RCTs, i.e. dietary counselling and face-to-face mindfulness, were concluded. Reviews of NPIs have called for lengthier follow-up assessments to evaluate if clinical outcomes were maintained from the initial non-pharmacological RCTs [59,60]. The LFC study did so accordingly, making this another key strength of the current study.

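### Hypothesis 4 is worded as an effect of taking part in earlier interventions and names no randomised arm or comparator; analysed that way, selection into the source trials could be read as a sustained intervention effect

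*Protocol article*

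**What the plan says.** The Introduction states the aim: "the study also examined if participation in previous NPIs from the CHI study would prevent cognitive decline and improve psychosocial outcomes". Hypothesis 4, under Research hypotheses, predicts that "participants who had been involved in NPIs from the CHI study would be likely to retain or show improvement in cognitive function and psychosocial outcomes". Both passages define the exposed group by having taken part.

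The Introduction also gives the origin of these interventions: "the CHI study acted as a recruitment platform for other randomized trials that investigate non-pharmacological interventions", with face-to-face mindfulness training and dietary counselling as examples. The Discussion again calls these two RCTs. It says of the LFC follow-up "This constituted a more rigorous evaluation of NPIs", on the ground that it shows whether effects lasted after the trials ended.

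The analysis is a single sentence in the Data analysis section: "linear-mixed modelling and multivariate regression analyses were employed to examine the individual and overall effects of NPIs on cognitive functioning and psychosocial outcomes". It gives model families and outcomes. Neither this sentence nor any other in the article says that participants are analysed by allocated arm, where control-arm members of the source trials are placed, or what the overall effect is made of.

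**The concern.** Whether a randomised effect is sustained is a question about the arms that were randomised. Participation is a different exposure. It depends on who was approached, who was willing and who was eligible for each trial, and those features may be related to later cognition and well-being whether or not the intervention works.

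Under the participation wording, a control-arm member of a source trial could be counted as involved, counted as not involved, or left out. Each choice gives a different estimate. The overall effect across several trials is likewise not a randomised contrast unless it is built from comparisons within each trial.

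At stake is the meaning of the result. The aim speaks of preventing decline and the Discussion of effects that persist. A selection difference between people who entered a trial and people who did not could be reported in those terms.

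**Working it through.** **1. The passages side by side**

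| Element | Where | What it fixes |
|---|---|---|
| Exposure in the aim | Introduction | participation in earlier NPIs |
| Exposure in hypothesis 4 | Research hypotheses | involvement in NPIs; no comparator named |
| Source of the NPIs | Introduction, Discussion | randomised trials recruited from CHI |
| LFC design | Introduction | prospective cohort, no new randomisation |
| Analysis | Data analysis | mixed models and multivariate regression; no arm, trial or comparator |
| Interpretation | Introduction, Discussion | prevention of decline; effects sustained after the RCTs |

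The exposure (row 2) and the interpretation (row 6) do not match unless the analysis uses the arms implied by row 3. The article does not say that it does.

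**2. The plan's own figure**

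The only sample-size figure, under Study sample and participation criteria, is 550, for multiple regression with three predictors, f² = 0.02, α = 0.05 and 80% power. Using the overall F test with 3 and N − 4 degrees of freedom and noncentrality 0.02 × N, the smallest N is 550 (power 0.801). The figure reproduces. It says nothing about the hypothesis 4 contrast and serves below only as a total N.

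**3. What baseline adjustment can and cannot do**

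Write the follow-up score as baseline + 3 × annual change. Conditioning on the CHI baseline removes a group difference in starting level. If trial entrants would have declined more slowly anyway, by δ per year, and that is unrelated to baseline, a difference of 3δ remains with no intervention effect. A residual gap of 0.2 SD corresponds to δ = 0.2 / 3 = 0.067 SD per year.

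**4. Illustration of size (assumptions, not figures from the article)**

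Assume N = 550, a participant share q, no true NPI effect, and a residual selection gap d in SD units of the quantity tested, after any baseline adjustment.

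SE = √(1/(Nq) + 1/(N(1 − q)))

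P(p<0.05) = Φ(d/SE − 1.96) + Φ(−d/SE − 1.96)

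For d = 0.2:

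- q = 10% (55 v 495): SE = 0.142, d/SE = 1.407, probability 0.291
- q = 20% (110 v 440): SE = 0.107, d/SE = 1.876, probability 0.467
- q = 30% (165 v 385): SE = 0.093, d/SE = 2.149, probability 0.575

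Over the same shares, d = 0.1 gives 0.108 to 0.189 and d = 0.3 gives 0.560 to 0.897. With d = 0 the probability is 0.05.

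**5. Precision of the arm-based comparison**

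Detectable difference at 80% power = (1.960 + 0.842) × √(2/n per arm). With an assumed 30, 60 or 100 followed up per arm this is 0.72, 0.51 or 0.40 SD. Detecting 0.2 SD needs 393 per arm.

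**The case against.** The strongest reply is that the analysis sentence names no contrast at all. A reader might infer that the randomisation has been discarded and that non-participants are the LFC comparator. The documents do not support that. The one phrase that points to such a comparator, "cognitive improvements as compared to control participants who did not participate in NPIs", describes a cited five-year follow-up and not LFC, and it may simply mean that study's own control group. Being involved in an NPI could be read as having been allocated to it. Estimating individual effects is compatible with trial-by-trial contrasts.

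Nor is the Discussion's claim of greater rigour an overclaim for a participant comparison. In context it refers to the longer follow-up of the trials.

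The article condenses a fuller protocol and perhaps an analysis plan, either of which could specify the arms. A mixed model using CHI scores would remove differences in starting level, and everyone in LFC had already volunteered for CHI and agreed to be re-contacted, which narrows the selection contrast. The article gives no evidence on how trial entrants differ from the rest of the cohort.

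All of this stands, and it limits the point to a conditional one. It does not remove it. The exposure is stated twice in words of participation, and no sentence says that allocation is the analysis variable. If an arm-based analysis is intended, the aim and the hypothesis describe the wrong exposure and need correcting.

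**Conclusion.** The concern holds in conditional form. The article frames hypothesis 4 as an effect of participation, gives no arm or comparator, and attaches a causal conclusion to interventions that came from randomised trials. If the analysis is done as worded, selection into the trials could be read as a sustained effect. The part that matters most is selection related to rate of decline, which baseline scores leave in place.

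The size cannot be established, because the article gives no counts per trial or arm. The range of about 29% to 57.5% rests on an assumed residual gap of 0.2 SD, an assumed participant share of 10% to 30%, and a simple two-group test on 550 people. It shows that a modest gap would matter, not that one exists. The change is worth making before the hypothesis 4 results are reported; the article says that analyses are still under way.

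**What to change.** - State the main hypothesis 4 estimate as the comparison of randomised arms within each source trial, as allocated, adjusted for the CHI baseline value of the outcome.
- Say where control-arm members are placed.
- Define the overall effect as the pooled within-trial contrast, for example with trial as a fixed effect.
- Report LFC follow-up by arm. Attendance is a further selection step: people who could not be contacted, had a dementia diagnosis or fell below the MMSE consent threshold are not followed, so the arm comparison is protected only as far as loss is similar between arms.
- Keep any participant versus non-participant contrast as secondary, adjusted for baseline cognition, age, education and health. Describe it as an association, without the language of prevention.
- Reword the aim and hypothesis 4 to match, and record when the choice was made relative to the ongoing analyses.

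The cost is linking the trials' allocation lists to LFC identifiers, and wider intervals from the smaller N. With the per-arm numbers assumed above, only differences of about 0.40 to 0.72 SD would be detectable at 80% power, so the intervals should be reported and a null result should not be read as loss of effect.
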